#### Secondary hypothesis

The secondary hypothesis is that the magnitude of the brain inflammatory response will predict the quantity of specific brain injury markers (phospho-tau, NfL, neurogranin, synaptotagmin, SNAP-25) measured in the CSF. The strength of inter-relationship between the inflammatory and injury markers outlined will be examined using correlation coefficients. These will also be adjusted for potential confounding factors using partial correlation coefficients.

Analysis of the samples will take place at UEA, Trinity College Dublin and the University of Gothenburg. Should additional information become available during the course of the study, we will ensure that we use the most appropriate analysis available to answer the research questions.
CSF will be analysed for a number of inflammatory and neuronal injury markers. These include, but are not limited to: TNF-α, IL-1RA, IL-1β, IL-6, sTREM2, YKL-40, T-tau, P-tau, Aβ38, Aβ40, Aβ42, neurogranin, synaptotagmin and SNAP-25;Blood collected pre-operatively and at 48 h (± 4 h) will be analysed for TNF-α, IL 1RA, IL-1β, IL-6, T-tau and NfL;Blood collected pre-operatively will also be genotyped for the APOE ε2/ε3/ε4 polymorphism at UEA;PAXgene blood for later transcriptomic analysis looking for blood signatures that associate with, and may be predictive of, particular CSF and clinical outcomes in our patients.

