### Sample size

We will recruit 200 patients with dementia and hip fracture; and 200 patients without dementia but who have experienced a hip fracture. This sample size is pragmatically based upon what would appear to be achievable in the time available and with consideration of likely statistical power. Without adjustment, a sample size of 200 subjects per group will provide statistical power of 90% to detect a mean between group mean differences of 0.33 standard deviations in any outcome variable using a two-sided significance level of 5%. Assuming confounding variables entered into a General Linear Model ‘explain’ no more than 25% of the total variation (i.e. the co-efficient of determination, R2, is less than 0.25), then this sample size should provide 90%. Power to detect an ‘adjusted’ mean difference of around 0.37 residual standard deviations [27]. In either case, this would be deemed a relatively small effect to be detected with high probability.

Data will be collected initially from two different groups:
Group 1: Pre-operative acute hip fracture patients with confusion;Group 2: Pre-operative acute hip fracture patients without confusion.

In respect of Group 1 (those with confusion), the AMT (England) and 4AT (Scotland) score indicate that a patient may be living with dementia. However, this may not be confirmed until 1-month post-op when reviewing the patient’s case notes, contacting their GP or reviewing their relevant Suitable Informant’s IQCODE Scores. Based on prior research, we anticipate that up to 50% of patients who have an AMT score of 8 or less (England) or 4AT score of 1 or above (Scotland) will have dementia (diagnosed or undiagnosed/vectored) [22]. Therefore, up to 400 may need to be recruited to this group. Recruitment will be monitored and stopped for Group 1 as soon as we receive 200 patients with confirmed dementia required for the study.

We will also collect data from patients without confusion (Group 2), who are unlikely to be confirmed with dementia at 1-month post-op. These patients will be included in the non-dementia group. Again, recruitment will be monitored and stopped from this group once 200 non-dementia patients have been included. The number required from this group will be dependent upon the non-dementia confirmation rate for this group.

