There will be a number of patients from Group 1 (Pre-operative acute hip fracture patients with confusion) for whom we cannot find evidence of dementia at 1-month post-op. The samples and data from this (confused, non-dementia) group will be deposited into a biobank at the Norwich Biorepository, for use in future research studies. In cases where patients were initially in Group 2 (Pre-operative acute hip fracture patients without confusion) but where evidence of dementia is available at 1 month post-op, we will reallocate these patients to the dementia patient group.

Comparable data will also be provided from a third group (Oslo Cohort) of 200 ‘stable’ patients living with a confirmed dementia diagnosis, taken from existing memory clinic data (Norwegian Registry of Persons with Cognitive Symptoms (NorCog) (Reference: S-08143a and 2017/371). Samples for this group are already available, as lumbar puncture is part of the diagnostic workup of patients included in the Norcog registry (Reference: S-08143a). These samples were analysed in 2017 at Sahlgrenska for the following: Aβ38, Aβ40, Aβ42, 10xAb42/Ab40, YKL-40, IL-1β, IL-6, IL-8, TNF-α, G36-NG2. The respective regional committee responsible have already provided permission to compare these results with those gathered in the present study.

Thus, we shall assemble data from 3 groups (hip fracture and dementia, hip fracture and non-dementia, stable and dementia), each with an expected 200 subjects. Please (see Fig. 1: Study diagram and group allocation of patients).

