#### Primary hypothesis

We will address the primary hypothesis, that systemic inflammation arising from hip fracture leads to an acute brain injury, by comparing the level of inflammatory and neuronal injury CSF and blood markers between the three groups defined above. Accordingly, we predict raised inflammatory and injury markers for the confirmed dementia-hip fracture group compared to the medically stable dementia group (Oslo cohort) and compared to the non-dementia hip fracture group.

Each of the markers will be compared across groups using a general linear model with the marker as the dependent variable (i.e. a separate model for each biomarker). The initial model will simply include group as an explanatory factor. A further model will then be constructed, including potential confounding variables, such as age, to provide an adjusted between group mean difference (comparing fracture patients with dementia to fracture patients without and fracture patients with dementia to stable dementia patients), together with 95% confidence intervals and significance test. In the event of the residuals for these models not appearing normally distributed, an appropriate transformation will be applied, such as a logarithmic transformation. We also predict that patients with dementia will have significantly worse cognitive and functional informant-based scores. A similar analysis will be conducted with cognitive and functional scores as the dependent variable.

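### For markers taken from the 2017 Oslo run, the contrast of fracture with dementia versus stable dementia cannot be separated from assay run

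*Protocol article*

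**What the plan says.** The Primary objective and the Primary hypothesis set two contrasts for fracture patients with dementia: against stable dementia patients, and against fracture patients without dementia. On the first, the Primary hypothesis section states: "we predict raised inflammatory and injury markers for the confirmed dementia-hip fracture group compared to the medically stable dementia group (Oslo cohort".

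The Sample size section describes the Oslo comparator. Of its samples it says "These samples were analysed in 2017 at Sahlgrenska for the following", and lists Aβ species and their ratio, YKL-40, IL-1β, IL-6, IL-8, TNF-α and G36-NG2. It adds that permission has been given to compare these results with those of the present study.

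The fracture samples follow another path. The Day of operation section has them frozen and held at the biorepository until final analysis. The Secondary hypothesis section then says: "Analysis of the samples will take place at UEA, Trinity College Dublin and the University of Gothenburg".

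The model is a separate general linear model per marker, with group alone and then with confounders, of which age is the named example. The three groups are "each with an expected 200 subjects".

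**The concern.** For a marker compared through its 2017 value, every Oslo measurement comes from one run and every fracture measurement from a later one. Kit lot, calibrator, operator and year, and possibly laboratory, all change exactly where group changes. Any shift between runs enters the estimated group difference one for one, in either direction: it could create an apparent fracture effect or hide a real one. A batch term in the model would be collinear with group, and age or other patient covariates carry no information about the run.

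This matters because the primary hypothesis is that inflammation from the fracture injures the brain. The other primary contrast compares fracture patients with fracture patients, so it cannot show an effect of fracture. Only the Oslo contrast can, and it is the exposed one. A large sample does not help: it narrows the interval around a biased value.

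**Working it through.** **Inputs from the Sample size section.** "a sample size of 200 subjects per group will provide statistical power of 90"% for "mean between group mean differences of 0.33 standard deviations in any outcome variable", "using a two-sided significance level of 5"%; and, assuming R² below 0.25, "Power to detect an ‘adjusted’ mean difference of around 0.37 residual standard deviations". The size of a run shift and the spread of each marker are not given and are assumed below.

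**Step 1: reproduce the plan's figures.**
- SE of a two-group difference = √(1/200 + 1/200) = 0.10 SD.
- Power at 0.33 SD = Φ(0.33/0.10 − 1.96) = Φ(1.34) = 0.91, against the stated 90%.
- Difference detectable with 90% power = (1.960 + 1.282) × 0.10 = 0.324 SD.
- Adjusted: 0.324/√(1 − 0.25) = 0.374, against the stated 0.37.

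Both figures hold.

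**Step 2: which markers are exposed.** The Primary objective names nine CSF markers.
- On the 2017 list: TNF-α, IL-1β and IL-6. Neurogranin is a fourth if G36-NG2 is that assay, which the article does not say.
- Not on the 2017 list: IL-1RA, NfL, T-tau, synaptotagmin and SNAP-25.

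So three, or at most four, of the nine are exposed. They include three of the four named inflammation markers.

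**Step 3: effect of a pure run shift.** Let the true difference be zero and the shift be s (in SD). The expected observed difference is then s, and

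P(p<0.05) = 1 − Φ(1.96 − s/SE) + Φ(−1.96 − s/SE).

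Unadjusted SE = 0.10. With the protocol's R² of 0.25, SE = 0.10/√0.75 = 0.115 residual SD.

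| Assumed shift | Unadjusted | Adjusted |
|---|---|---|
| 0.05 SD | 8% | 7% |
| 0.10 SD | 17% | 14% |
| 0.20 SD | 52% | 41% |
| 0.33 SD | 91% | 82% |
| 0.50 SD | >99% | 99% |

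An observed unadjusted difference of 1.96 × 0.10 = 0.196 SD is enough for significance.

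**Step 4: the same on a percentage scale.** For a log-transformed marker, a proportional calibration shift p equals ln(1 + p)/(log-SD) in SD units. Rates are unadjusted.

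| Assumed log-SD | 10% shift | 20% shift |
|---|---|---|
| 0.3 | 0.32 SD, 89% | 0.61 SD, >99% |
| 0.5 | 0.19 SD, 48% | 0.36 SD, 95% |
| 1.0 | 0.10 SD, 16% | 0.18 SD, 45% |

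The risk depends strongly on the marker's spread: a 10% shift is serious for a tight marker and modest for a widely spread one.

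**The case against.** Several stronger readings are tempting, and the article does not support them.

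- **That group is aliased with batch throughout the design.** It is not. Fracture with versus without dementia lies wholly within the newly collected samples, and nothing stated aliases that contrast with run.
- **That every Oslo value dates from 2017.** Five of the nine primary CSF markers have no listed Oslo result. Either Oslo material will be newly assayed for them, when a shared run is possible, or they have no Oslo comparator, which is a separate matter.
- **That each marker is spread over three laboratories.** Three institutions are named for all sample work, including APOE genotyping at UEA. No marker is said to be split, and how Sahlgrenska relates to the Gothenburg site is not stated. A shared laboratory would remove the site difference but not the difference between 2017 and a later run.
- **That a false finding is to be expected.** It could occur. How often depends on a shift and a spread that the article does not give.

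The best defence is that this is an article. Plate layout, calibrators and bridging controls commonly sit in a laboratory manual, full protocol or SAP, and their absence here is no finding. The Abstract also speaks of comparing with existing samples, and the Sample size section calls the Oslo samples available, so re-assay is not excluded. That stands as far as it goes. But the Sample size section goes further than silence: it presents the 2017 results as what will be compared. If the assays are run on that basis, no later analysis plan can recover the contrast.

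**Conclusion.** The concern holds for the primary contrast of fracture with dementia versus stable dementia, and for the markers whose Oslo values come from the 2017 run: TNF-α, IL-1β and IL-6, plus neurogranin if G36-NG2 is that assay. YKL-40 and the Aβ measures, which are on both the 2017 list and the planned CSF panel, are exposed in the same way if compared with Oslo. For these markers the contrast is fully confounded with run, and possibly with laboratory, and covariate adjustment cannot undo it.

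The probabilities follow from the protocol's own 200 per group, a normal approximation and an assumed shift. A shift as large as the design effect would usually be declared significant, one of 0.20 SD about half the time, and one of 0.10 SD about one time in six.

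**What to change.** In the Sample size section, and where sample analysis is described under the Secondary hypothesis, state for each marker used in the Oslo contrast that:

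- stored Oslo aliquots, or a random bridging subset of them, are assayed in the same laboratory and campaign as the fracture samples, with groups mixed across plates;
- if only a subset is re-run, the 2017 values are recalibrated from the paired results, and the calibration error is carried into the confidence interval of the group difference;
- where neither is possible, the Oslo contrast for that marker is reported as descriptive and is not attributed to fracture.

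This has to be settled before the fracture samples are assayed. The cost is kits and stored volume; no new patients or procedures are needed. It is conditional on two things that the article does not establish: that usable Oslo volume remains after the 2017 work, and that the permission, which is described as covering comparison of results, extends to re-assay. The descriptive fallback needs neither, but gives up the inferential claim about fracture for that marker.

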## Discussion

Despite significant investment, disease-modifying treatments for dementia are still absent and there has been no significant treatment breakthrough for 15–20 years [28]. Inflammation is a vital part of the immune system’s response to injury and infection which may become harmful if exaggerated or unresolved. There is now growing evidence that harmful inflammation in the brain is aetiological and contributed to the pathophysiology of dementia [29].

Recent research highlights acute illnesses or injuries that cause inflammation throughout the body, such as infection, trauma and surgery, can accelerate the speed of decline in dementia [30, 31]. For example, an infection in a hospitalised older person with dementia is linked to a higher long-term worsening of that person’s symptoms. The underlying mechanisms linking inflammation, cognition and dementia progression remain greatly under-researched, with almost no studies in humans. This lack of research impacts on the search for new treatments targeting inflammation in dementia.

Thus this study will develop understandings of the role of inflammatory response in dementia and support developing pharmaceutical interventions. Additionally it will inform ways to predict deterioration in dementia. Exploration of new potential disease pathways remains essential for finding new therapeutic targets.

## Data Availability

Not applicable.

## Abbreviations

AMTS: Abbreviated Mental Test Score
ARUK: Alzheimer’s Research UK
BTP: Best Practice Tariff
CSF: Cerebrospinal fluid
DMEC: Data Monitoring and Ethics Committee
EDTA: Ethylenediaminetetraacetic acid
GP: General Practitioner
IQCODE: Informant Questionnaire for Cognitive Decline in the Elderly
MMSE~ 2: SV: Mini-Mental State Examination - 2nd Edition, Short-Form version
NHFD: National Hip Fracture Database
NHS: National Health Service
NOF: Neck of femur
PDPH: Post-dural puncture headache
SAP: Statistical Analysis Plan
SMG: Study Management Group
SSC: Study Steering Committee
UK: United Kingdom
